### Additional consent provisions for collection and use of participant data and biological specimens {26b}

Not applicable, this trial does not collect biological specimens.

## Interventions

### Explanation for the choice of comparators {6b}

On completion of the baseline assessment, participants will be randomised to either the RELAX intervention alongside UC or UC alone. The research team will send a letter via NHS.Net email, containing details about the trial and outlining the participant’s involvement to their GP and midwife/maternity service. For participants recruited outside of a participating NHS site (e.g. via social media), the midwife/maternity services letter will be given to the participant to pass on to their midwife. For participants at the NHS recruitment sites, their participation will be recorded in the electronic clinical notes.

### Intervention description {11a}

#### Active arm – RELAX + usual care (UC)

Participants in the active arm will complete 12 sessions (approximately 15–20 min duration) of the RELAX intervention via the online platform using a computer, laptop or tablet, in the 4 weeks post-randomisation. Participants will be asked to complete their first session within 24 h of the baseline assessment. Participants will be able to choose when to complete the remaining sessions, although instructions on the platform will encourage them to complete 3 sessions per week. Participants will not be able to complete more than one session per day (unless they completed part of a session the previous day, in which case they can complete that session the following day alongside a new session).

#### Usual care (UC)

Usual care typically involves monitoring by maternity services and contact with a health visitor. Women may also be offered information on self-referral to local psychology services, where they will typically be put on a wait list or be offered generic interventions (e.g. group treatment, computerised CBT). Those in the control arm will only receive usual care and when they log onto the RELAX platform after T0, they will only see information regarding their next assessment, which will become active for completion on the date they are scheduled to open.

#### RELAX session description

The sessions involve listening to 30 pre-recorded audio descriptions of ambiguous everyday situations (scenarios) that can be interpreted in both negative and positive ways and are pertinent to the daily lives of pregnant women. Approximately 50% of the scenarios describe situations that occur in pregnancy, e.g. attending medical appointments, managing pregnancy symptoms, preparing for baby and the transition to motherhood.

The scenarios were developed with feedback and input from women with lived experience of perinatal anxiety, via focus groups and individual interviews. In addition, we drew on themes of worries and anxiety commonly reported during pregnancy, identified in the research literature [18]. All scenarios were developed by trained and expert research team members ([name]), and a proportion of the scenarios checked for suitability and clinical accuracy by both the RELAX PPIE group and midwives in the wider research team.

Worry scenarios tend to focus on worry about the future, whilst rumination scenarios tend to focus on events from the past. Across the 30 scenarios presented per session, approximately 60% are worry focussed and 40% rumination focussed. In order to provide a mix of scenarios per session, half of the scenarios were not pregnancy related but were carefully selected for suitability for pregnant women and drawn from scenarios used Hirsch et al. [27].

The scenarios are all ambiguous and involve uncertainty. The ambiguity can be resolved in either a positive or negative manner. The scenarios are designed such that the ambiguity is either resolved for the participant with a positive interpretation provided (positive scenarios), or the ambiguity is left unresolved (ambiguous scenarios), and the participant is required to generate a positive outcome for the situation. Positive scenarios are always presented earlier in the session than ambiguous ones. As the sessions progress, participants are presented with increasing numbers of ambiguous scenarios; 50% in sessions 1–4, 70% sessions 5–8 and 90% sessions 9–12.^2^ Furthermore, in sessions 1 to 5, some positive scenarios are presented again but in their ambiguous form, in order to help participants to generate a positive interpretation themselves (examples provided in Table 1).

**Table 1 Tab1:** Examples of RELAX ambiguous intervention scenarios

Positively resolved scenario	Comprehension question
You are at a routine ultrasound scan. It is taking longer than you expected. The sonographer is very quiet, but from her face you know she thinks things are fine	Do you think that the sonographer has found a problem?
You are going to visit a friend for the weekend but are thinking about cancelling as you have not been feeling great recently. You decide to still go as you don’t want to let your friend down. On the journey back home, you reflect on the weekend and realise visiting your friend was worthwhile	Do you regret going to visit your friend?
You realise how many things you have left to prepare for the arrival of your baby and decide to write down things you can do this weekend to make a start. Doing this makes you feel calmer	Was making a list of things to do a bad idea?
It is your birthday approaching, and the first birthday where you have been pregnant. As you think about being a year older you think about your current situation and are filled with a sense of satisfaction	Are you thinking positively about your birthday this year?
Ambiguous scenario	Comprehension question
You are at a routine ultrasound scan. It is taking longer than you expected. The sonographer is very quiet, but from her face you know what she is thinking	Will the sonographer tell you that there is a problem?
You are attending a pregnancy exercise class and you are following the class quite well this week. At a break there is a chance to talk to other women attending, who all seem to know each other. As you approach them, you can tell whether you will be included in the conversation	Was it hard to join in the conversation with the group?
You talk with a friend about what she did to connect with her baby during pregnancy. She enthusiastically gives you some ideas and you think over whether they will be helpful or not	Will your friend’s suggestions be useful for connecting with your baby?
A friend is talking to you about how she is feeling during her pregnancy, and you start dwelling on the fact that you have both have completely different symptoms. You wonder what that could mean about your pregnancy	Does it matter that you have different symptoms to your friend?

There are 30 trials per session (scenario, comprehension question and rating). For each trial the participant listens to the scenario and imagines themselves in positive outcome of the situation. Participants are then prompted to answer either yes or no to a subsequent comprehension question designed to reinforce the positive interpretation. Participants receive accuracy feedback with a tick or cross depending on accuracy of the response provided. For 50% of the trials, participants will then be asked to rate how they experienced the scenario on a visual analogue scale from 0 (not at all positive) to 100 (extremely positive). For the remaining 50% of trials, participants will be asked to rate how vividly they were able to imagine the ending on a scale from 0 (not at all vivid) to 100 (extremely vivid). Written feedback will be presented on the screen and will be dependent upon the ratings that participants provide (e.g. “Good effort!”, “That’s great!”).

#### Training to use the intervention

The first session will last approximately 30 min, whilst the remainder are 15–20 min duration.

In session 1, participants will be presented with brief videos that outline the rationale for training, and details about how to complete training sessions and how to schedule their sessions. Participants will be asked to complete the sessions in a space free of distractions, ideally using headphones to enable them to be immersed in the scenarios. To facilitate positive imagery generation, participants will complete a one-off imagery training. This will involve watching a short video about imagery and completing imagery exercises, as per Hirsch et al. [27]. Participants will then practice imagining positive outcomes of the scenarios and answering questions, after which they will complete the 30 trials. At the end of the first session, participants will complete expectancy ratings of how logical the intervention seems on a scale of 0 (not logical at all) to 4 (very logical) and how useful they expect it to be on a scale of 0 (not at all useful) to 4 (very useful).

Sessions 2 to 12 will comprise 30 trials and take between 15 and 20 min to complete. At the end of session 3, participants will be asked to notice when they are thinking negatively in day-to-day life and then try to identify a potential positive outcome for the situation. The goal of this is to help participants generalise the training into daily life. Participants will also be sent a text message the day after sessions 3, 6 and 9 to remind them to try and identify positive outcomes when they notice themselves worrying or thinking negatively about a situation.

A minimum of 20 telephone interviews will also be conducted with participants allocated to the RELAX condition. This nested qualitative study will include participants who complete all, some or none of the RELAX sessions. In addition, we will include participants who withdrew from the sessions in order to determine their views of the intervention and to provide them with an opportunity to suggest ways in which it could be improved.

### Criteria for discontinuing or modifying allocated interventions {11b}

Participants will be informed that they are free to withdraw from the trial completely or discontinue with their RELAX sessions at any time.

### Strategies to improve adherence to interventions {11c}

Alerts have been designed to automatically nudge participants if they have left a session incomplete, e.g. they will receive a reminder the next day and can be able to finish the session that day (and can complete their next full session that same day if they wish). Participants will also receive email reminders from the RELAX platform to complete sessions if they have not completed the target number of sessions by a particular time, e.g. if less than 3 sessions have been completed by the end of week 1. Researchers monitoring progress will contact participants via phone call, email or text message (SMS) if they are progressing through sessions too slowly, so that they will be able to complete them all within the required timescale. Researchers will help troubleshoot any issues participants may be experiencing regarding the scheduling of sessions or technical issues.

### Relevant concomitant care permitted or prohibited during the trial {11d}

Participants in both trial arms will continue to receive usual maternity care. They may be offered information about how to self-refer to local psychology services where they will be put on a waiting list or be offered generic interventions (e.g. group treatment, computerised CBT) or advised to contact their GP, who may signpost them to counselling services and / or discuss medication.

As usual care may potentially involve being offered psychological treatment, individuals who are currently receiving or have recently received psychological treatment will not be excluded from the trial. Engagement in current psychological interventions at any point during the trial will be monitored and information for this requested at each follow-up assessment. The RELAX intervention will not be available outside of the trial, so there is no risk of the UC arm being exposed to the intervention or other CBM-I interventions given that they are also not currently available in the UK.

### Provisions for post-trial care {30}d

There are no provisions for post-trial care as a part of this study.

### Outcomes {12}

#### Clinical outcomes

The primary outcome is the mean difference in anxiety (measured using GAD-7) at 8 weeks post-randomisation between arms, adjusting for anxiety at baseline. For secondary outcomes, we will measure the mean differences between arms in:Anxiety (GAD-7) at 36 weeks post-randomisationDepression (PHQ-9) at 8 weeks post-randomisation and 36 weeks post-randomisationRNT (RTQ-10 (trait)) at 8 weeks post-randomisation and 36 weeks post-randomisationTrait worry (PSWQ) at 8 weeks post-randomisation and 36 weeks post-randomisationPerinatal depression (EPDS) at 8 weeks post-randomisation and 36 weeks post-randomisationPerinatal anxiety (PASS) at 8 weeks post-randomisation and 36 weeks post-randomisationWork and social functioning (WSAS) at 8 weeks post-randomisation and 36 weeks post-randomisation

#### Mechanistic outcome

The primary mechanistic outcome is the mean difference in interpretation bias (measured using the Recognition Test) at 4-week post-randomisation between arms, adjusting for baseline interpretation bias. The mediating effect of the intervention on GAD-7 at T2 via interpretation bias at T1 will also be evaluated.

### Participant timeline {13}

At the point of enrolment into the study all participants will be between 16 and 28 weeks pregnant. Participants will be enrolled in the study for approximately 9 months in total (Fig. 1). Participants in the intervention arm will have 4 weeks from the point of randomisation to complete the 12 RELAX sessions.

**Fig. 1 Fig1:**
[figure not shown]
RELAX trial flow diagram

#### Follow-up assessments

There are 4 assessments yoked to randomisation that all participants are required to complete: baseline pre-randomisation (T0; 16–28 weeks gestation); 4 weeks post-randomisation (T1; end of intervention for active arm; 20–32 weeks gestation); 8 weeks post-randomisation (T2; 24–36 weeks gestation), and 36 weeks post-randomisation (T3; 12–24 weeks post-birth).

### Sample size {14}

#### Clinical efficacy sample size

For a two-sided independent samples *t*-test, alpha = 0.05, assuming one baseline and three post-randomisation measures with correlation rho = 0.5 (conservative based on baseline − T2 estimate from Hirsch, Krahe et al., 2021 [27] of rho = 0.42), deflation factor of 0.5 [45], and accounting for 35% attrition (based on online CBT: [46]), we will need 268 participants in total (134 per arm) to have 90% power to detect a GAD-7 effect size of 0.35 (powered slightly conservatively compared to T2 GAD-7 effect size of 0.40 from Hirsch, Krahe et al., 2021 [27]).

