#### Analysis of primary and secondary clinical outcomes

The mean difference in GAD-7 between arms at 8 weeks post-randomisation will be estimated using a mixed-effects linear analysis of covariance (ANCOVA) model with repeated measures and a random intercept at the participant level. We will include as dependent variables the GAD-7 scores at 4 weeks, 8 weeks (primary outcome) and 36 weeks post-randomisation. We will also adjust for trial arm, time, baseline anxiety (GAD-7), weeks of gestation at baseline (a pre-specified baseline variable), the three randomisation stratification variables, and an interaction term for trial arm and time to allow effects to differ over time and be extracted at the different time points. Furthermore, if any baseline variables are found to predict missing outcome data, we will include them as covariates in our model. The mean differences between arms for the GAD-7 at 36 weeks secondary outcome will be estimated using the model described for the primary outcome, with the mean differences between arms for the other secondary outcomes estimated using similar models to those described for the primary outcome.

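### The stated 90% power needs a variance deflation factor of 0.5 that does not apply to the single 8-week GAD-7 contrast; at the plan's own 35% attrition, 268 participants give about 72–76%

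*Protocol article*

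**What the plan says.** The section on the clinical efficacy sample size bases the calculation on a two-sided independent-samples t-test at alpha 0.05, "assuming one baseline and three post-randomisation measures with correlation rho = 0.5 (conservative based on baseline" to T2 estimate of 0.42 from an earlier trial of the same type of training). It then applies a deflation factor of 0.5, supported only by a citation, and 35% attrition taken from online CBT. It concludes that "we will need 268 participants in total (134 per arm) to have 90% power to detect a GAD-7 effect size of 0.35", and describes 0.35 as slightly cautious against the 0.40 seen at T2 in the earlier trial.

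The section on clinical outcomes fixes the target: "The primary outcome is the mean difference in anxiety (measured using GAD-7) at 8 weeks post-randomisation between arms", adjusted for baseline anxiety. The section on the analysis of primary and secondary clinical outcomes estimates it from a random-intercept model for the 4-, 8- and 36-week scores, with "an interaction term for trial arm and time to allow effects to differ over time and be extracted at the different time points". Nowhere is the primary effect defined as an average over the follow-up visits.

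**The concern.** A deflation factor that rewards several follow-up measures is valid when the treatment effect being tested is pooled over those measures. Here it is not. The arm-by-time interaction gives each visit its own treatment effect, and only the 8-week one is primary. The power statement therefore describes a different analysis from the one planned.

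Two further points in the same section do not fit. The factor of 0.5 does not follow from the stated "one baseline and three post-randomisation measures" under the usual baseline-adjusted formula. And rho = 0.5 is presented as the cautious choice against 0.42, when for a baseline-adjusted comparison it is the more favourable one.

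At stake is how a non-significant primary result is read. Under the stated power, a true effect of 0.35 would be missed one time in ten. If the true figure is about 72–76%, it would be missed about one time in four, and a null result would carry much less evidence against a benefit of that size than the protocol implies.

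**Working it through.** **Inputs from the protocol article.** Two-sided alpha 0.05; effect 0.35 SD; rho 0.5 (cited estimate 0.42); deflation factor 0.5; attrition 35%; 134 per arm; 1:1 allocation.

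**Step 1: reproduce the stated figure.** The exact (noncentral t) sample size for 0.35 SD with 90% power is 173 per arm. Then 173 × 0.5 = 86.5, rounded up to 87; 87 / 0.65 = 133.8, rounded up to 134 per arm, 268 in total. The plan's figure is reproduced, and it depends wholly on the 0.5.

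**Step 2: what the factor should be.** Assume equal correlations between all measures, as a single rho and a random intercept imply. The baseline-adjusted variance of the mean of r follow-ups, relative to one unadjusted measure, is

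(1 + (r − 1)·rho)/r − rho²

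| Follow-ups averaged | rho = 0.50 | rho = 0.42 |
|---|---|---|
| 1 (the 8-week visit alone) | 0.750 | 0.824 |
| 2 | 0.500 | 0.534 |
| 3 (as stated) | 0.417 | 0.437 |

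With complete data and a full arm-by-time interaction, the 4- and 36-week scores add no precision to the 8-week contrast, so its factor is the first row, 1 − rho². A factor of 0.5 for a single visit would need rho = √0.5 ≈ 0.71, which the protocol does not claim. The value 0.5 matches two averaged follow-ups, not the three stated.

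**Step 3: power for the planned contrast.** Analysed per arm: 134 × 0.65 ≈ 87. Exact t-test power at effect 0.35/√factor:

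- factor 0.5 (as stated): 90.1%
- factor 0.75 (rho 0.5): 0.35/√0.75 = 0.404, power 75.5%
- factor 0.8236 (rho 0.42): 0.35/√0.8236 = 0.386, power 71.5%

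The normal approximation gives 76.0% and 72.0% for the last two. With 87 per arm, the effect detectable with 90% power is 0.43 (rho 0.5) or 0.45 (rho 0.42). Power at the cited effect of 0.40 is 86% or 82%.

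**Step 4: sample size that 90% would have needed at 35% attrition.** 173 × 0.75 = 129.75 → 130; 130/0.65 = 200 per arm, 400 in total. At rho 0.42: 173 × 0.8236 = 142.5 → 143; 143/0.65 = 220 per arm, 440 in total.

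**Step 5: sensitivity to attrition at week 8.** The protocol gives one attrition figure and does not split it by visit. Power for 0.35, counting only those observed at week 8:

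| Loss at week 8 (assumed) | rho = 0.50 | rho = 0.42 |
|---|---|---|
| 35% | 76% | 72% |
| 25% | 81% | 78% |
| 20% | 84% | 80% |
| 10% | 88% | 85% |
| 0% | 91% | 88% |

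**Step 6: what the mixed model recovers.** Participants missing at week 8 but seen at other visits contribute a little. With 35% missing at week 8 and everyone seen at week 4, power is 77.6% (rho 0.5) or 73.4% (rho 0.42). With everyone seen at both week 4 and week 36 it is 78.4% or 74.1%. Under an assumed staged loss leaving 103 per arm at week 8 and 87 at week 36, it is 83.2% or 79.5%.

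**Step 7: direction of the rho assumption.** Moving rho from 0.42 to 0.5 lowers the factor in every row of the Step 2 table. It also does so if 0.5 was obtained as 1 − rho (0.58 to 0.50). The choice of 0.5 therefore reduces the calculated sample size.

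**The case against.** The strongest reply is about certainty and size.

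- **Source of the 0.5.** The formula is not shown, so tracing it to an averaged-follow-up calculation is an inference; it also equals 1 − rho. This stands, but the conclusion does not depend on the source: 0.5 is not the factor for one baseline-adjusted visit at rho 0.5.
- **Attrition.** The 72–76% puts the whole 35% loss at week 8, although follow-up runs to 36 weeks and the protocol describes payments, reminders and repeated prompts. This also stands. A 20% loss would give 84% or 80%. But 90% is regained only at rho 0.5 with a loss of no more than 3–4%, and not at all at rho 0.42.
- **Number of follow-ups.** On the averaged reading, using 0.5 instead of 0.417 errs on the safe side (94% power, or 226 participants for 90%). That is right. The mismatch shows the stated inputs and factor do not agree; it is not itself evidence of low power.
- **Rho.** The wrong direction costs only about 4 percentage points. True, but it is wrong as written under every candidate formula.
- **Other covariates.** Gestation and the stratification factors may add precision. The protocol does not quantify this, so it cannot be counted.
- **Consequence.** Neither the estimand, the model nor the confidence interval changes, and power at 0.40 is still 82–86%. This limits the damage to the power claim and to readings that lean on it.

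**Conclusion.** The concern holds. The 90% power is not a property of the planned primary analysis. On the plan's own inputs, 268 participants give about 76% power for 0.35 at rho 0.5 and about 72% at the cited rho of 0.42. The effect detectable with 90% power is 0.43–0.45, above the 0.40 cited as prior evidence, so the description of 0.35 as a cautious target is not borne out.

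These figures assume that the full 35% attrition applies at week 8, that 0.35 is in units of the unadjusted SD, that correlations are equal across visits, and that covariates other than baseline GAD-7 add nothing. Relaxing the attrition assumption raises power but reaches 90% only with almost complete 8-week data at rho 0.5. The description of rho = 0.5 as conservative is wrong in direction regardless of these assumptions.

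**What to change.** Keep N = 268 and restate the calculation for the 8-week contrast in the protocol, and in the SAP wherever it repeats it:

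- use the factor 1 − rho², with rho = 0.42 (0.82) as the main case and rho = 0.50 (0.75) as the optimistic one;
- state about 72–76% power for 0.35, about 82–86% for 0.40, and 90% for about 0.43–0.45, all at 35% loss by week 8;
- add the power at the 8-week retention actually achieved, since the 35% is not split by visit;
- remove the claim that rho = 0.5 is conservative, and either drop the deflation factor of 0.5 or give its formula and the analysis it belongs to.

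The cost is a text correction and a less favourable stated power. No participants are added, and the primary outcome and model stay as they are.
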